### Randomization

Following baseline assessments (see Fig. 1 and Measures section below for details), participants are randomized into either of the two study arms using a pre-programmed randomization module in REDCap. Randomization is site-specific to ensure balance within site. After randomization, participants randomized to the PrEP for Health intervention condition can elect to have their initial intervention session with the PrEP Navigator that day or schedule an appointment for a later date.

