Ongoing PrEP navigation support: For three months after the initial intervention session, PrEP Navigators provide additional, ongoing MI and PrEP navigation, as needed, through in-person, phone, and text-based interactions to support participants in coping with ongoing or new challenges with PrEP uptake, adherence, and persistence. Near the end of this three-month period, PrEP Navigators’ help participants plan for ongoing PrEP adherence and persistence.

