### Statistical analyses

Planned preliminary analyses include assessing distributions and autocorrelations across time for all variables. As we are utilizing interviewer-administered survey assessments, the primary anticipated reason for missing data is participant attrition. Based on our preliminary studies, we are anticipating and accounting for 20% attrition. Attrition effects will be evaluated by testing whether systematic differences exist between participants who complete the research study and those who discontinue participation. We will explore strategies (e.g., multiple imputation) for imputing missing data based on patterns of missingness, using sensitivity analyses to determine the optimal method of handling missingness. Dependent variables will be examined to determine which distributional models are most appropriate for subsequent statistical procedures. We will examine the equivalence of the random assignment with regards to key baseline characteristics, including socio-demographics and risk behaviors.

Aim 1: Our primary analysis will compare PrEP uptake and adherence (co-primary outcomes) between the PrEP for Health intervention and eSOC conditions. For PrEP uptake, we will perform chi-square tests to examine group differences in proportions over the course of the study, and Cox proportional hazard models to assess differences in time to PrEP initiation. For PrEP adherence, we will initially assess differences in adherence at 3-month follow-up visits. We will also conduct longitudinal analyses to assess differences in adherence over the course of the study (12 months). We will use generalized linear models (GLMs) with properly chosen link functions. GLMs will be estimated using generalized estimating equations with robust standard error estimates (GEE), which provide an extension of regression analysis to the case of correlated or repeated observations and allows for inclusion of both categorical (e.g., binomial) and count-dependent variables (e.g., Poisson, zero-inflated) and appropriate modeling of covariance structures when observations are correlated across time. We will follow an intent-to-treat model, analyzing participants according to the study arm to which they are assigned, regardless of fidelity to assigned group. Sensitivity analyses will compare those who receive the intervention session(s) to those who do not. All analyses will use two-tailed tests of significance, with significance at alpha level 0.05.

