### Sample size calculations

The primary power analysis was based on differences between the PrEP for Health intervention and eSOC conditions in PrEP uptake (co-primary outcome). Effect sizes are estimated from our pilot studies, as well as results of a large mathematical modeling study examining PrEP use among U.S. PWID [87]. Assuming baseline uptake at 25%, with uptake of 50% in the PrEP for Health intervention arm (effect size: d = 0.60), we need 80 completers per condition to have 90% power to find a significant difference at alpha = 0.05. Assuming 20% attrition, we will need to enroll 200 PWID (100 per arm).

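### The sensitivity analysis by session receipt is a confounded as-treated contrast that is likely, though not certain, to favour the intervention and does not test the robustness of the ITT result

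*Protocol article*

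**What the plan says.** All of the following is in the protocol article.

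- **Primary analysis set** (Statistical analyses, Aim 1): "We will follow an intent-to-treat model, analyzing participants according to the study arm to which they are assigned, regardless of fidelity to assigned group".
- **Sensitivity analysis** (next sentence): "Sensitivity analyses will compare those who receive the intervention session(s) to those who do not". The article does not say whether the non-receivers are intervention-arm non-attenders only or also the control arm. It does not say which session counts, and it names no adjustment.
- **Testing rule** (same paragraph): "All analyses will use two-tailed tests of significance, with significance at alpha level 0.05". As worded, this covers the sensitivity contrast too.
- **How attendance arises** (Randomization): after allocation, intervention participants "can elect to have their initial intervention session with the PrEP Navigator that day or schedule an appointment for a later date".
- **Second session** (PrEP for Health Intervention condition): Module 2 is for participants who have initiated PrEP. Those who have not initiated within a month may instead repeat Module 1.
- **Navigation** (same section): "For three months after the initial intervention session, PrEP Navigators provide additional, ongoing MI and PrEP navigation".

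**The concern.** Whichever comparator is meant, the groups are formed by sessions received and not by assigned arm, so randomisation no longer protects the comparison. The article itself gives reasons to expect confounding. Its Background ties low service engagement and low PrEP uptake to low perceived risk, low interest, homelessness and incarceration. The same factors would plausibly keep people away from in-person sessions.

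The second session adds another problem. Its Module 2 is given because the participant has already started PrEP, so counting it as exposure lets the outcome help define the exposure. In the planned Cox model of time to initiation, grouping people by later attendance also introduces immortal-time bias.

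A sensitivity analysis should vary an assumption behind the main estimate, such as missing data, model form or outcome definition. This contrast varies none of them; it estimates something else. At stake is interpretation: an as-treated difference tested at 0.05 and labelled a sensitivity analysis could be taken as support for the ITT result, or as an offset to a null one.

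**Working it through.** **1. The plan's own figures.** Sample size calculations states "Assuming baseline uptake at 25%, with uptake of 50% in the PrEP for Health intervention arm (effect size: d = 0.60"), that "we need 80 completers per condition to have 90% power to find a significant difference at alpha = 0.05", and "Assuming 20% attrition, we will need to enroll 200 PWID (100 per arm"). With the pooled-variance formula, n per arm = [1.96·√(2·0.375·0.625) + 1.2816·√(0.25·0.75 + 0.50·0.50)]² / 0.25² = (1.342 + 0.848)² / 0.0625, which rounds up to 77. With 80 per arm the power is 91.2%. Enrolment is 80 / 0.80 = 100 per arm. The stated d matches ln(3)·√3/π = 0.606. The design reproduces and is not in question.

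**2. Set-up for the contrast.** From the plan: 100 per arm and 25% control uptake. Assumed: sessions have no effect, so uptake is 25% in both arms; a proportion *a* of the intervention arm attends; attenders are *R* times as likely as non-attenders to start PrEP. The documents give neither *a* nor *R*.

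- Non-attender uptake: p_n = 0.25 / (aR + 1 − a)
- Attender uptake: p_a = R·p_n
- All non-receivers pooled: p_c = [100(1 − a)·p_n + 100·0.25] / [100(1 − a) + 100]
- Spurious difference: p_a − p_c (pooled) or p_a − p_n (within the intervention arm)

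**3. Worked case, a = 0.70 and R = 2.** p_n = 0.25 / 1.7 = 14.7% and p_a = 29.4%. p_c = (30·0.147 + 25) / 130 = 22.6%.

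- Pooled: 29.4 − 22.6 = +6.8 points. The chance of a positive estimate is 85%, and of a falsely significant positive result 19%.
- Within arm: 29.4 − 14.7 = +14.7 points, with chances of 96% and 33%.

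**4. Range.** Pooled difference in points, with the chance of a falsely significant positive result in brackets (nominal 2.5%; normal approximation):

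| R | 50% attend | 70% attend | 90% attend |
|---|---|---|---|
| 0.67 | −6.6 (0.1%) | −5.0 (0.3%) | −2.1 (1.0%) |
| 1 | 0.0 (2.5%) | 0.0 (2.5%) | 0.0 (2.5%) |
| 1.5 | +6.7 (16%) | +4.3 (10%) | +1.6 (4%) |
| 2 | +11.1 (36%) | +6.8 (19%) | +2.4 (6%) |
| 3 | +16.7 (64%) | +9.6 (33%) | +3.2 (8%) |

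A simulation with 40,000 replicates per setting (R of 1 and above) agrees closely with the table. On the same simulated data the ITT difference averages 0, with a two-sided error of about 5%.

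**5. The alternative under the same null.** The complier average causal effect is the ITT risk difference divided by the proportion of the intervention arm receiving session 1. Under the null it is 0 / 0.70 = 0, whatever R is. The price is precision. The ITT standard error is √(2·0.25·0.75/100) = 0.061, so the complier standard error is about 0.061 / 0.70 = 0.087 and the 95% half-width about 17 points. The pooled as-treated contrast has standard error √(0.294·0.706/70 + 0.226·0.774/130) = 0.066 and half-width about 13 points, but around a biased centre.

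**The case against.** - **Direction is not assured.** A reader might infer that the contrast must come out positive even if the sessions do nothing. The documents do not support that. It requires R above 1, which is plausible but nowhere quantified. Each session carries a $10 payment (Overview of study design), so need for money as well as motivation could drive attendance. At R = 1 there is no bias, and below 1 the sign reverses. This objection stands.
- **Size may be small.** The first session can take place on the day of randomisation and is paid, so attendance could be high. At 90% attendance and R = 2 the pooled bias is 2.4 points and the chance of a positive estimate only 65%. This stands for the pooled comparator. Within the intervention arm the same setting still gives 13.2 points (26.3% against 13.2% before rounding).
- **ITT is primary.** A reader might infer that the efficacy test is compromised, or that the authors intend to claim a dose-response. Neither is supported: the primary comparison, its error rate and its power are untouched, and no such use is announced.
- **The article condenses.** Comparator, definition of receipt and any adjustment may be set out in a fuller document, and their absence is not the point. What the article does state is the choice to compare by receipt and the label it gives that comparison. Adjustment could reduce the confounding but would not restore randomisation.
- **A complier effect does not test ITT either.** True. It rescales the ITT difference into another estimand, so it should be reported as supplementary and not called a sensitivity analysis. Its conditions are also inferred: the article does not say outright that controls receive no sessions or that attendance is logged.

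**Conclusion.** The point holds in a limited form. Carried out as written, the planned contrast compares groups formed after randomisation, is open to confounding, and is partly driven by the outcome if the second session counts. It says nothing about the robustness of the ITT estimate.

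Under a true null, with 50-90% attendance and R from 1 to 3, the spurious pooled difference lies between 0 and about 17 points, against a planned true difference of 25 points (50% minus 25%). Attendance and R are assumptions. An upward bias is the likelier direction, given what the article says about barriers to engagement, but neither its sign nor its size can be read from the documents. The consequence is confined to how a supplementary result is labelled and interpreted.

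**What to change.** 1. **For PrEP uptake, replace the contrast with a complier average causal effect.** Use randomised arm as the instrument and receipt of session 1 as the exposure, and report it as a supplementary estimand beside ITT. Defining receipt by session 1 avoids the Module 2 problem.
2. **Confirm the conditions first.** Check that no control participant received a session and that attendance is recorded for every intervention participant. The design makes both plausible: both arms see the video, navigation support is timed from the first session, and sessions are paid individually. State the remaining assumption that assignment affects uptake only through session 1.
3. **Limit this to uptake.** Adherence is assessed only among those who report initiating PrEP, so the same ratio would not be randomisation-based for that outcome.
4. **If any receiver versus non-receiver comparison is kept,** label it exploratory and non-causal, and state the comparator and which session counts.

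The cost is a change of wording in the analysis plan and a little extra analysis, with a wider confidence interval than the as-treated contrast (about ±17 against ±13 points in the worked case). Trial conduct and sample size do not change.

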### Sample size calculations

The primary power analysis was based on differences between the PrEP for Health intervention and eSOC conditions in PrEP uptake (co-primary outcome). Effect sizes are estimated from our pilot studies, as well as results of a large mathematical modeling study examining PrEP use among U.S. PWID [87]. Assuming baseline uptake at 25%, with uptake of 50% in the PrEP for Health intervention arm (effect size: d = 0.60), we need 80 completers per condition to have 90% power to find a significant difference at alpha = 0.05. Assuming 20% attrition, we will need to enroll 200 PWID (100 per arm).

### Data management, safety and monitoring

All survey data is inputted directly into REDCap, a HIPAA-compliant, comprehensive data management system. Hard and soft-copy participant data is identified by an ID number only, and a link between names and ID numbers is kept separately in a password-protected file. Name-based files are stored separately from survey data. Soft copy data is stored on study-specific secure and password protected network drive folders and is only accessible to study staff. Hard copy data is stored in locked cabinets within restricted and secure areas at study sites.

All study staff are trained in confidentiality and have signed confidentiality agreements. Study staff have been trained in ethical human subject research practices to minimize participant risk. The investigators report unanticipated problems, safety monitors’ reports, and adverse events to the Fenway Health IRB in accordance with IRB policies.

Given that this is a behavioral intervention with minimal risk, the study has no stopping rules and interim analyses will not be conducted. An independent Data Safety Monitoring Board has been assembled and reviews study progress, including safety concerns and adverse events, twice per year. All reports are shared with the IRB and the funder at least annually.

### Dissemination plan

In addition to reporting on clinicaltrials.gov, findings from this study will be disseminated via peer-reviewed publications and conference abstracts/presentations. Moreover, presentations at community organizations, including our partner SSP sites, and government entities (e.g., local public health departments, CDC) will be conducted. We will also create easy-to-read infographics to share via social media and our research group website(s).

## Discussion

In the context of rising HIV transmission among PWID nationally, [1–4] improved use of evidence-based HIV prevention strategies is urgently needed. Though PrEP (in the form of daily oral antiretroviral medications) has been approved for use for more than a decade, uptake among PWID has been stagnant and numerous hypothesized PrEP adherence and persistence challenges exist [26, 27]. From our formative research, we learned that interventions needed to address multiple, multilevel barriers to PrEP utilization among PWID, including low HIV knowledge and perceived risk, limited PrEP knowledge and interest, and interpersonal, clinical, and structural barriers to healthcare utilization [26, 27]. Drawing from Social Cognitive Theory (SCT) and evidence on the benefits of patient navigation, we selected individually tailored education, motivational interviewing, problem-solving and planning, and ongoing navigation support as our key intervention strategies. To test the efficacy of the PrEP for Health intervention in improving PrEP uptake, adherence, and persistence among PWID, we designed the RCT described in this paper in close collaboration with our community partner organizations (SSPs) in two communities in MA that have been heavily impacted by opioid and polysubstance use and injection-related HIV transmission. We believe our resulting study design has several key strengths and innovations, including our community-informed approach, our rigorous yet “real-world” study design, and the flexibility of our intervention to evolving modalities, as described below.

First, in addition to selecting intervention strategies and a delivery format supported by behavioral theory and evidence from our formative research, we also received critical input from our community research partner organizations (SSPs). Importantly, we learned that most—if not all—of the theory- and evidence-based strategies we selected were feasible and culturally appropriate within SSP contexts. For example, many SSPs already provide PrEP information and screening services (e.g., HIV testing) that can support the initial stages of the PrEP care continuum. Similarly, we learned that MI is well-aligned with SSPs’ harm reduction-orientation and models of client-centered service delivery. In terms of intervention delivery, we also received community input on the need for primarily in-person research activities. Despite the restrictions imposed by the COVID-19 pandemic on research activities and SSP services, we were aware that a large proportion of our study population lacks consistent phone and Internet access. Thus, to reach a wide swatch of local PWID and ensure that some of the most marginalized individuals (i.e., those completely lacking phone and Internet access) were not excluded, we temporarily delayed study initiation during COVID-19-related closures of our SSP sites to eventually launch an in-person study with appropriate safety measures in place.

Similarly, while we initially considered delivering all intervention content and strategies within a single session, our SSP research partners advised us to split the content across two sessions of more limited length (i.e., ≤ 45 min) to reduce participant burden. Upon implementing the study, we also learned that referrals from SSPs to nearby PrEP prescribers, along with participants’ decisions to initiate PrEP, can often require days to weeks, so our separation of the intervention content into two sessions, spaced approximately one month apart, enabled the first session to focus on PrEP uptake and the second session to either revisit that content or proceed on to PrEP adherence and persistence, depending on participants’ needs. These two sessions, in addition to being more manageable for interventionists and participants, thus enabled more specific attention to key barriers and plans relating distinct steps in the PrEP care continuum. Anecdotally, we have also observed how the scheduling and planning required for the second session promotes continued interaction and rapport between interventionists and participants.

Second, to enhance scalability if PrEP for Health is found to be efficacious, we designed a rigorous yet “real-world” intervention to help maximize widespread implementation. Our study takes place in two distinct sites in terms of inner (i.e., organizational) and outer contextual (i.e., community) factors. While our intervention and assessment procedures are identical across sites, we worked with our SSP research partners to develop recruitment and retention protocols to maximally engage participants in the study; while we use most of our recruitment and retention activities in both sites, differences in the communities (e.g., in terms of urban density, availability of public transportation options) have required regular reconsideration of which strategies to prioritize in each site. By being in constant community with our SSP research partners through regular all-team meetings and daily interactions with study staff, we have also been able to improve our referral processes, for example, by ensuring that staff are present on days when PrEP prescribers are onsite or in nearby mobile clinics. Maintaining flexibility in some aspects of our approach based on our understanding of real-world organizational and community factors (e.g., changing our study schedule to be present on days when mobile clinics are nearby) has supported implementation of the trial so far.

Third, we have remained aware of recent advances in biomedical HIV prevention technologies and were pleased that cabotegravir received U.S. FDA-approval for use as long-acting injectable as PrEP (LAIP). Research by our team and others has found LAIP to be preferred over daily oral PrEP in several PWID samples because it would eliminating the need for adherence to a daily medication, which is particularly challenging for PWID who frequently experience homelessness, forced residential relocation, incarceration, and loss or theft of personal belongings including medications [26, 27, 32, 88, 89]. Despite this important advantage of LAIP, there are still notable barriers to initial uptake (one of our primary outcomes) and hypothesized challenges with PrEP persistence (our secondary outcome). As such, if local prescribers begin prescribing LAIP in the communities where our participants reside as part of their clinical standard of care, it will be available to them, and we will continue to track their PrEP uptake, adherence and persistence outcomes. We have considered how the flexibility of our intervention content, which was designed to be tailored to individuals’ unique needs, can be responsive to evolving PrEP modalities. Furthermore, from all participants, we are collecting data on interest in LAIP (via surveys) which can support future research or programmatic efforts to increase availability of this modality to PWID, who have unfortunately been excluded from much PrEP research to date, including efficacy trials of injectable PrEP [24].

### Limitations

There are potential limitations of the proposed project. First, the RCT may not be powered to determine intervention efficacy for our secondary outcome of PrEP persistence; however, findings may still help inform subsequent research. Second, by situating this study within two urban SSPs in Massachusetts, findings may not generalize to other geographic regions or PWID who do not access SSPs. However, our selected SSP sites cover distinct metropolitan areas and are community-based venues frequented by large numbers of PWID who are diverse in terms of race, ethnicity, age, gender, and sexual orientation, possibly enhancing the generalizability of findings. Moreover, our mediation and moderation analyses will provide more insight into both mechanisms of action and subgroup differences that can inform future broadening in scope. Finally, although this study will not directly address issues of cost-effectiveness of PrEP for PWID, implementation-related findings could inform research on other health interventions for this medically underserved population.

